## Abstract

**Background:**

Intensive treadmill training (TT) has been documented to improve gait parameters and functional independence in Parkinson’s Disease (PD), but the optimal intervention protocol and the criteria for tailoring the intervention to patients’ performances are lacking. TT may be integrated with augmented virtual reality (AVR), however, evidence of the effectiveness of this combined treatment is still limited. Moreover, prognostic biomarkers of rehabilitation, potentially useful to customize the treatment, are currently missing. The primary aim of this study is to compare the effects on gait performances of TT + AVR versus TT alone in II-III stage PD patients with gait disturbance. Secondary aims are to assess the effects on balance, gait parameters and other motor and non-motor symptoms, and patient’s satisfaction and adherence to the treatment. As an exploratory aim, the study attempts to identify biomarkers of neuroplasticity detecting changes in Neurofilament Light Chain concentration T0-T1 and to identify prognostic biomarkers associated to blood-derived Extracellular Vesicles.

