Regarding non-motor symptoms, cognitive impairment may associate or even precede motor symptoms in PD and can worsen over time from mild cognitive impairment to full-blown dementia during the disease course. Drugs give limited benefits to this disorder, making it essential to explore the effects of non-pharmacological approaches (13). Targeted cognitive training presents some evidence of effectiveness in patients with initial impairment, but a recent review suggests that TT produces even greater cognitive effects (14). Virtual reality (VR) is used in the motor and cognitive training of patients with various neurological diseases, including PD. VR refers to a computer-generated three-dimensional digital environment that can be explored and interacted with by a person. Augmented reality or augmented virtual reality (AVR) is the union between VR and real life. The person who experiences it can interact with virtual content in the real world. Computer-generated content is superimposed on reality through visual stimuli such as objects and films, tactile and olfactory sensations, and sounds. AVR is proposed as an interactive approach, that aims to amplify the effects of motor training, both directly and indirectly, increasing the patient’s motivation and satisfaction, promoting greater adherence and participation to treatment, and training also cognitive aspects of fall risk (14). For these reasons, AVR is considered an emerging and promising therapeutic tool in neurorehabilitation (15). In this regard, positive results emerged from the clinical trial of Gulcan et al. (16) in which AVR-VR TT has been demonstrated to be effective in PD on most of spatial–temporal gait parameters compared to conventional physical therapy.

Moreover, results from recent reviews dedicated to comparing the benefit of VR rehabilitation, including TT, versus conventional one showed that VR appears to be promising in motor outcomes such as gait and mobility (17–19), obtaining the most replicated and convincing result on balance (18–21); less evidence has been reported on functional autonomy (19) and QoL (18).

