### Outcome measures

2.6

The primary outcome is the difference in gait performance assessed by the POMA-G scale between the TT+AVR and the TT group at T1. The secondary outcomes are differences in mobility (measured by POMA-G at T2 and POMA-B at T1 and T2), in kinematic gait parameters assessed at T1 and T2, measured by the Optogait system, differences in other motor and non-motor symptoms at T1and T2, patients’ satisfaction, assessed with a 5-point Likert scale, and adherence to the treatment.

Exploratory outcome measures include changes in NfL concentration and change in individual Raman spectra of blood-derived cEVs before and after treatment. The correlation between Raman spectra of blood cEVs and the rehabilitation outcome will be assessed (the biological characterization of patients at T0 analyzing cEVs performed by Raman Spectroscopy will provide numerical scores that will be correlated with motor parameters obtained after treatment to identify prognostic biomarkers of rehabilitation outcome).

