#### Data analysis

2.7.2

Statistical analysis will be conducted using the software SPSS v28 (Armonk, NY: IBM Corp). The distribution will be assessed using the Kolmogorov–Smirnov test for all clinical and instrumental continuous data, assuming the presence of normal distribution when *p* > 0.05. Data will then be summarized as mean and standard deviation, median and interquartile range, or absolute and percentage frequency, as appropriate.

The experimental and the control groups will be compared at baseline to explore significant differences in demographic, clinical, and instrumental variables. Parametric or non-parametric tests will be used for continuous variables, according to data distribution. The chi-square test will be used to compare distributions of binary/categorical variables.

Both within and between-group analyses will be conducted to assess at each time point the effects of the treatments delivered, for primary and secondary outcome measures. Specifically, a two-way repeated measures ANOVA will be used with a within-factor (time of assessment) and a between-factor (group).

Regarding biological data, the acquired Raman spectra will be analyzed by multivariate Principal Component Analysis – Linear Discriminant Analysis (PCA-LDA) classification. PCA will reduce the number of variables into principal components, which will be used to build the LDA model. The model will be built to discriminate clinical improvement detected as quantifiable change on clinical scales, defined based on the minimum clinically important difference, when available from the literature. The sensitivity, specificity, and accuracy of the predicting model based on spectra data will be assessed. In addition, correlation analysis will be conducted to evaluate the association between spectral data and change on clinical scales recorded between the treatment’s beginning and end. Statistical analysis of the Raman data will be performed using Origin2023b (OriginLab Corporation, Northampton, MA, USA) (34).

Univariate analysis models will be used to select the best prognostic markers of clinical improvement to be included in a multivariate model.

For all analyses, statistical significance will be set at *p* < 0.05.

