Pain is a frequent non-motor symptom in PD, contributing significantly to disability and reduced QoL. It affects around 67.6% of PD patients versus 15–30% of the general population. The most frequent pain syndromes in PD are musculoskeletal pain, neuropathic radicular pain, dystonia-related pain, akathitic discomfort, and primary central parkinsonian pain (78). Among clinical scales suitable to assess pain intensity, the NRS scale is simple, well-validated, and easy to use for clinicians and to understand for patients. The NRS is a recommended tool for assessing pain intensity in the general population and is widely used also in PD, although it is cautiously recommended in this population because it is not disease-specific (78).

Experience appreciation will be estimated for both treatment groups using a 5-point Likert scale and correlated with the level of adherence to the treatment. Indeed, independently of the effectiveness on motor symptoms, results coming from previous studies suggest a higher appreciation of VR training by the patients compared to the conventional TT which is perceived as monotonous or boring, and less useful to integrate into their daily life environment (79–81). Thus, satisfaction will be tested to confirm these findings. Along with adherence to either treatment, and to the evaluation of the possibly different clinical and instrumental effect of either intervention, this measure can provide relevant information on potential barriers and motivators for exercise and rehabilitation. Indeed, as to accessibility to these services, while the TT is currently available in most rehabilitation facilities, TT associated to AVR is more expensive and less available. As to motivators, AVR is claimed to be a relevant motivator (14): our study will allow us to investigate this issue, by allowing a comparison of both adherence and patients’ satisfaction in either intervention. Thus, our study may provide highly relevant information about the superiority of TT + AVR versus TT, to potentially provide grounds to expand the adoption of TT + AVR instruments, even if this may be associated to generally higher costs.

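### No adjustment for randomised arm is stated for the exploratory prognostic analyses or the satisfaction–adherence correlation; for T0 markers this costs power, for post-randomisation pairs it can produce a correlation

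*Protocol article*

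**What the plan says.** In section 2.7.2 (Data analysis) a group factor is named for one model, the two-way repeated measures ANOVA of the primary and secondary outcomes. The biomarker work is then described without it:

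- A PCA-LDA classifier is built on principal components of the Raman spectra: "The model will be built to discriminate clinical improvement detected as quantifiable change on clinical scales".
- Next to it, "correlation analysis will be conducted to evaluate the association between spectral data and change on clinical scales", the clinical change being that from the start to the end of treatment. The sentence does not say whether the spectra are those at T0, those at T1 or their change.
- Markers are screened one at a time, and those selected go into a multivariate model whose covariates are not listed.
- All tests use p < 0.05.

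Section 2.6 (Outcome measures) is clearer on one use. The T0 spectra "will provide numerical scores that will be correlated with motor parameters obtained after treatment to identify prognostic biomarkers of rehabilitation outcome". It also lists "change in individual Raman spectra of blood-derived cEVs before and after treatment" as an exploratory outcome.

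The Discussion adds: "Experience appreciation will be estimated for both treatment groups using a 5-point Likert scale and correlated with the level of adherence to the treatment". The same paragraph notes that "results coming from previous studies suggest a higher appreciation of VR training by the patients compared to the conventional TT", and the Introduction describes AVR as "promoting greater adherence and participation to treatment". No size is given for either effect.

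**The concern.** The outcome these analyses try to explain, clinical improvement, is one that the trial expects the allocated treatment to move. Followed as written, they do not take out that source of variation. What this does depends on when the two variables are measured.

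- **T0 marker against a later outcome.** Randomisation makes the marker independent of arm. Leaving arm out adds removable noise to the outcome, so a true marker is harder to detect.
- **Two variables measured after randomisation.** Arm can shift both. A correlation then appears across the whole sample even if the two are unrelated within each arm.

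Satisfaction with adherence is the clearest case of the second kind, because the article itself expects AVR to raise both. A positive correlation could then be read as satisfaction motivating adherence when it shows only which treatment was received. The same applies to spectra against clinical change, if T1 or change spectra are meant.

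**Working it through.** **1. The plan's own figure (section 2.2).** POMA-G after 4 weeks in an earlier study: 10.7 (SD 1.1) and 11.7 (SD 0.5).

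- Pooled SD = √((1.1² + 0.5²)/2) = √0.73 = 0.854, so d = 1.0/0.854 = 1.17.
- A two-sided two-sample t-test at 0.05 with 20 per arm has power 0.950. The stated 20 per arm is reproduced.
- Enrolment is 48. With 20% dropout, 48 × 0.8 = 38.4, so about 38 are evaluable. The planned evaluable number is 40.

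**2. T0 marker, outcome shifted by arm.** Equal arms; d is in within-arm SDs.

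- Share of outcome variance due to arm = (d²/4)/(1 + d²/4). At d = 1.17 this is 0.342/1.342 = 25.5%.
- Correlation over the whole sample = within-arm r/√(1 + d²/4). At d = 1.17 the factor is 0.863, so r = 0.40 becomes 0.345. At d = 0.5 the factor is 0.970, so it becomes 0.388.
- Power by Fisher z, two-sided 0.05, n = 38:
  - with arm: atanh(0.40) × √34 = 0.424 × 5.83 = 2.47, power about 70%;
  - without arm, d = 1.17: atanh(0.345) × √35 = 0.360 × 5.92 = 2.13, power about 57%;
  - without arm, d = 0.5: atanh(0.388) × √35 = 0.410 × 5.92 = 2.42, power about 68%, a loss of about 2 points.
- At N = 40 and d = 1.17, for within-arm r of 0.3, 0.4 and 0.5, power falls from 0.46, 0.72 and 0.91 to 0.36, 0.59 and 0.80.
- With no true link (r = 0) and d = 1.17, the simulated false-positive rate without an arm term is 0.05. Allocation creates no link with a T0 marker.

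**3. Two post-randomisation variables, unrelated within arm, shifted by d₁ and d₂.** The documents give no size for either shift, so the values below are assumptions spanning a range.

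Induced r = (d₁/2)(d₂/2)/√((1 + d₁²/4)(1 + d₂²/4)); rejection rates at p < 0.05 are from 40,000 simulated trials per row.

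| Shift in both (SD) | Induced r | Rejection, N = 40 | Rejection, N = 48 | With arm term |
|---|---|---|---|---|
| 0.5 | 0.0625/1.0625 = 0.06 | 6% | 7% | 5% |
| 0.8 | 0.16/1.16 = 0.14 | 14% | 16% | 5% |
| 1.17 | 0.342/1.342 = 0.25 | 37% | 43% | 5% |

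With unequal shifts of 0.5 and 1.17 SD the rejection rate at N = 40 is 12%; with 0.8 and 1.17 SD it is 22%.

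**The case against.** The strongest reply is that much of this is read from silence. No sentence says the arms are pooled. The article condenses a longer plan, the covariates of the multivariate model are not listed, and an analysis plan that is not shown may include arm. The Discussion speaks of satisfaction in both treatment groups and of comparing the interventions, so correlations by group may be intended. This stands in part: the point is about what is written and cannot be put as a decision to pool. But a group factor is named for the ANOVA, while the marker screening is called univariate and the other analysis is a plain correlation. Followed literally, both are unadjusted, and screening comes before any adjusted model.

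Four stronger readings are tempting, and the documents do not support them.

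- A reader might infer that allocation can make T0 spectra look prognostic. It cannot, because randomisation makes them independent of arm.
- A reader might take d = 1.17 as the arm effect on every variable here. The article gives it only for post-treatment POMA-G, from an earlier study of partial weight-supported treadmill training against conventional gait training. It gives no such figure for change scores, spectra, satisfaction or adherence.
- A reader might assume that spectral change is correlated with clinical change. The article does not say so; the time point of the spectra is unclear.
- From "Moreover, prognostic biomarkers of rehabilitation, potentially useful to customize the treatment, are currently missing" a reader might infer that the trial needs marker-by-arm interactions. The stated aim is prognosis, not choosing between the two treatments. With about 19 evaluable patients per arm, an interaction, or classifier accuracy reported by arm, would be too imprecise to require.

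**Conclusion.** The point holds in a limited form. As written, the univariate screening, the spectra-versus-change correlation and the satisfaction–adherence correlation carry no stated adjustment for arm.

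For T0 markers the consequence is lost efficiency without false links: about 13 points of power at r = 0.40 if the arm effect on the outcome were as large as 1.17 SD, and about 2 points if it were 0.5 SD. True markers become harder to find; it does not follow that they will be missed.

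For post-randomisation pairs the consequence is possible false association, ranging from negligible (6% against 5%) to serious (37%) depending on shifts that the documents do not quantify. Satisfaction with adherence is the most exposed, since the expected direction is stated for both. The spectral correlation is exposed only if T1 or change spectra are meant.

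These analyses are exploratory or descriptive. The between-arm comparisons of primary and secondary outcomes have their own group factor and are unaffected.

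**What to change.** In section 2.7.2:

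1. Include randomised arm as a covariate in the univariate screening models and in the multivariate prognostic model.
2. Use partial correlations given arm for satisfaction with adherence, and for any correlation that uses post-baseline spectra.
3. State whether T0, T1 or change spectra enter the correlation with change on the clinical scales.

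Arm is known for every participant, so no new data are needed. The cost is a change of wording and one degree of freedom per model, out of about 38 to 40 evaluable patients. If the full analysis plan already includes arm, it is enough for the article to say so.

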**Conclusion:**

This study will provide data on the possible superiority of AVR-associated TT over conventional TT in improving gait and other motor and non-motor symptoms in persons with PD and gait disturbances. Results of the exploratory analysis could add information in the field of biomarker research in PD rehabilitation.

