
In summary, the evidence of the potential superiority of TT + AVR versus TT to improve gait in PD is still preliminary, and few studies include both clinical and instrumental gait measures, as it is instead recommended (3); further, an optimal TT(+AVR) protocol, customized to patients’ performances has not been established; finally, potential biomarkers of neuroplasticity and prognostic biomarkers are still under study.

Taking into account these considerations, the primary objective of this study is to compare the effects on gait performances of an integrated rehabilitation intervention before and after intensive rehabilitation with TT endowed of AVR, versus TT alone in patients with PD in II-III Hoehn and Yahr stage (35) with gait disturbances. The secondary objectives are to assess the effects of the interventions on balance performances, kinematic gait parameters and other motor and non motor symptoms immediately after treatment and at a 3-months follow up, and to assess the patient’s satisfaction and adherence to the treatment. The exploratory objective is to investigate potential serum biomarkers of neuroplasticity and prognosis.

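### Prognostic markers are to be selected by univariate models and refitted in the same roughly 40 patients, which biases the resulting model; performance should be corrected for optimism

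*Protocol article*

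**What the plan says.** The protocol article, section 2.7.2 (Data analysis), describes two routes to a prognostic marker.

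- **Marker selection.** "Univariate analysis models will be used to select the best prognostic markers of clinical improvement to be included in a multivariate model". The sentence gives no threshold, ranking rule or list of candidates. The section ends with a general rule: "For all analyses, statistical significance will be set at *p* < 0.05".
- **Raman classifier.** "PCA will reduce the number of variables into principal components, which will be used to build the LDA model". The model is to separate patients by clinical improvement, "defined based on the minimum clinically important difference, when available from the literature". Then: "The sensitivity, specificity, and accuracy of the predicting model based on spectra data will be assessed". The number of components is not given, nor are the patients on whom performance will be measured. The section cites an earlier Raman study for this analysis.

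The status of this work is clear. The Introduction says: "The exploratory objective is to investigate potential serum biomarkers of neuroplasticity and prognosis". Section 2.6 (Outcome measures) gives the purpose of correlating baseline spectral scores with post-treatment motor results as "to identify prognostic biomarkers of rehabilitation outcome". The abstract claims only this: "Results of the exploratory analysis could add information in the field of biomarker research in PD rehabilitation".

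Section 2.2 sets the sample at 20 per arm, raised to 24 per arm (48 in total) for about 20% dropout. This is sized for the primary outcome; the prognostic analysis has no sample size of its own.

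**The concern.** Univariate selection uses the outcome to decide which predictors are kept. A marker passes because its association in this sample is large, whether through signal or chance. When the survivors are refitted on the same patients, the model treats them as if they had been chosen in advance. Coefficients are then too large, p-values too small, and fit and discrimination too good. The bias arises under any outcome-based rule for picking the best marker, so it does not depend on the exact threshold. It is worst when patients are few and candidates many.

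This method is written into the plan; it is not a detail left open. The pool of possible candidates is also wide. Section 2.4 collects about 19 clinical and cognitive scores, seven gait parameters at two speeds, and sway in six conditions, with Raman spectra in addition. How many of these will be screened is not said.

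The classifier raises a related question. LDA accuracy measured on the patients used to build the model is optimistic, and increasingly so with more components.

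At stake is the credibility of the biomarker results, which the Discussion presents as a major innovation and a strength. The randomised comparison of the two training programmes is not at stake.

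**Working it through.** **1. How many patients are available (section 2.2).** The plan's own figure reproduces. Pooled SD = √((1.1² + 0.5²)/2) = 0.854, so d = (11.7 − 10.7)/0.854 = 1.17. A two-sided t-test at α = 0.05 with power 0.95 needs 19.99, that is 20 per arm or 40 in total. From 48 enrolled, 20% dropout leaves 48 × 0.8 ≈ 38. I use n = 40 below.

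**2. Chance of selecting at least one useless marker.** Inputs not in the article, hence assumptions: threshold 0.05 (borrowed from the general significance sentence), m independent candidates, none related to outcome. The formula is 1 − 0.95^m. To check it and obtain the fit, I simulated 4,000 noise datasets per row: n = 40, a continuous outcome, screening at p < 0.05, then a least-squares refit of the survivors.

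| Candidates m | 1 − 0.95^m | Simulated: at least one selected | Mean number selected | Mean apparent R² when one is selected | Mean R² over all datasets |
|---|---|---|---|---|---|
| 5 | 0.23 | 0.23 | 0.26 | 0.15 | 0.04 |
| 10 | 0.40 | 0.40 | 0.50 | 0.16 | 0.07 |
| 20 | 0.64 | 0.65 | 1.02 | 0.20 | 0.13 |
| 30 | 0.79 | 0.78 | 1.49 | 0.23 | 0.18 |

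The true R² is zero throughout. The reason is simple: at n = 40 the critical t on 38 degrees of freedom is 2.024, so a marker passes only if its sample R² is at least 2.024²/(38 + 2.024²) = 0.097. Everything selected therefore starts from about 10% apparent explained variance. One useless predictor fixed in advance would average 1/39 = 0.026.

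**3. The same with a binary outcome (half improved).** Over 2,000 noise datasets per setting, with 10, 20 and 30 candidates at n = 40, at least one marker was selected in 40%, 63% and 78%. When one was selected, the refitted model was itself significant in essentially every run. Mean apparent AUC was 0.73, 0.75 and 0.77, and mean accuracy 0.67, 0.68 and 0.70, where 0.50 is the truth for both.

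**4. PCA-LDA on noise.** Assumptions: one spectrum per patient, two equal classes, 3 to 20 components. There were 300 simulated datasets per setting for accuracy on the building sample, and 100 for 5-fold cross-validation with PCA refitted inside each fold.

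| Components | Same patients, n = 40 | Same patients, n = 48 | Cross-validated, n = 40 |
|---|---|---|---|
| 3 | 0.60 | 0.59 | 0.49 |
| 5 | 0.64 | 0.63 | 0.51 |
| 10 | 0.72 | 0.70 | 0.49 |
| 15 | 0.78 | 0.75 | 0.50 |
| 20 | 0.84 | 0.80 | 0.49 |

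Cross-validation returns the figure to chance. Evaluation on the same patients does not, and the gap depends heavily on the number of components.

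**The case against.** Several points on the other side have force.

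- **The validation scheme may exist.** A condensed article can leave it to the full protocol, an analysis plan or the cited Raman method, none of which is at hand. The article says performance will be assessed, not on whom. A reader might infer that the accuracy figures will be resubstitution figures; the text does not say so. This stands, and that part is a request to state the scheme, not an error shown.
- **The 0.05 screening threshold is not stated.** A reader might take the closing significance sentence as the selection rule. The selection sentence names no rule, so 0.05 is an assumption here. The bias exists under any outcome-based rule; only its size would change.
- **The candidate pool is unknown.** Thirty is an unfavourable value. With 10, most noise datasets select nothing, and correlated candidates lower the effective number. A reader might also count NfL as a prognostic candidate, but the Discussion pairs NfL with neuroplasticity and vesicles with prognosis.
- **False markers are not certain.** Even with 30 null candidates about 22% of datasets select none, and 3 to 5 components give only 60% to 64% apparent accuracy. It would go too far to say the plan must produce good-looking markers from noise.
- **Repeated spectra.** Treating several spectra per patient as independent would make matters worse, but nothing in the article says this will be done.
- **The work is exploratory**, and the abstract's claim is modest. This limits the seriousness. It does not make selection followed by refitting a sound method, and the article sets the same significance level for all its analyses.

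**Conclusion.** The point holds in a limited form. The stated procedure, univariate selection followed by a multivariate refit in the same roughly 40 patients, biases coefficients, p-values and apparent performance. If screening is at 0.05 and candidates are independent and null, the chance of at least one false marker runs from about 23% (5 candidates) to 78% (30). The apparent R-squared of about 0.15 to 0.23 applies only to datasets where a marker was selected; averaged over all datasets it is about 0.04 to 0.18. Threshold and candidate number are assumptions, so these are ranges and not predictions for this trial.

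For PCA-LDA, the article does not state how performance will be validated. If it were measured on the building sample, noise would give about 60% to 84% at n = 40 for 3 to 20 components and equal classes. This shows why the scheme must be stated; it does not show that validation is absent from the trial's full documentation.

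The change is worth making but not critical. The primary comparison and the sample size are untouched.

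**What to change.** 1. **Replace univariate selection.** Before outcome data are examined, fix a short list of candidate markers and the outcome they are to predict. Enter them together in one model that includes treatment arm and baseline score. The model may be penalised (ridge or elastic net) or fully prespecified without selection; either removes the problem of screening and refitting.
2. **Report optimism-corrected performance** for that model, by bootstrap or cross-validation, with every data-driven step repeated in each resample.
3. **State the validation scheme for PCA-LDA.** Report sensitivity, specificity and accuracy only from patient-level cross-validation, with PCA and the choice of component number redone inside each fold. If a patient contributes more than one spectrum, keep them all in the same fold. If the full protocol or the cited Raman method already does this, one sentence saying so is enough.

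The cost is modest analyst time and no new data. The reported accuracy will probably be lower, and with about 40 patients it will remain imprecise even after correction.
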